### Data analysis

The two primary hypotheses of this study, which focus on comparing outcomes between groups for gambling and drinking respectively, will be analyzed using linear mixed-effect models with random intercepts. This will allow us to use all available participant data within the models, employing a restricted maximum likelihood to handle missing data. Separate analyses will be conducted for each primary outcome variable (i.e., NODS score, mean number of day gambled in the past month, and, for drinking, the number of drinks consumed in a typical week). For secondary analyses, mixed-effects models will be conducted to examine the effect of moderators on primary variables, that is, additional fixed-effect interactions will be included in exploratory models (e.g., extent of intervention use, participants’ sex, severity of gambling and drinking at baseline, and co-occurrence of mental health concerns). In addition, secondary analyses will also examine predictors of treatment use, as well as the effect of accessing treatment on primary outcomes. The third hypothesis, comparing the potential moderating effect of reductions in drinking on gambling severity, will be examined using Hayes’s Process macro. This method uses a state-of-the-art regression-based conditional process approach [41] to estimate covariances, variances, and means. Missing data will be handled using a maximum likelihood approach. Finally, we will examine whether changes in quality of life are related to improvements in gambling outcomes.

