### Major research questions

The proposed trial will compare the efficacy of two Internet interventions: an intervention that just targets gambling issues (G-only) versus one that contains an intervention for problem drinking in addition to an intervention for gamblers (G + A). Outcome variables for gambling will measure the reduction in gambling severity and frequency of gambling. The outcome for a reduction in alcohol use will be measured by the reduction in the frequency of drinking during the past week. The primary hypotheses are:**Hypothesis 1:** For problem gamblers with co-occurring problem drinking, it is predicted that participants provided access to the G + A website will display significantly reduced gambling outcomes at the 3- and 6-month follow-ups compared to those provided access to the G-only website. For problem gamblers without co-occurring problem drinking, there will be no significant difference between those provided access to the G-only and G + A websites at the 3- and 6-month follow-ups.**Hypothesis 2:** For problem drinkers, it is predicted that participants provided access to the G + A website will display significantly reduced drinking outcomes at the 3- and 6-month follow-ups compared to those provided access to the G-only website. For participants who are not problem drinkers, there will be no significant difference in drinking between those provided access to the G-only and G + A websites at the 3- and 6-month follow-ups.**Hypothesis 3:** Problem gamblers with co-occurring problem drinking who receive the G + A intervention and reduce the amount they drink between the baseline and 3-month follow-ups will display significantly improved gambling outcomes at the 6-month follow-up compared to problem drinkers who receive the G + A intervention but experience no decrease in their drinking.

Follow-ups at 3 and 6 months were chosen as it is unknown whether the intervention will have the predicted impact, and we wished to optimize the possibility of finding an effect by employing a short-term follow-up.

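### H1 and H2 are conditional on problem drinking, but the primary models name no problem-drinking term or contrast and the power statement covers only the whole-sample arm difference

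*Protocol article*

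**What the plan says.** **Hypotheses (Protocol article, Major research questions).** H1 has two limbs. The first reads "For problem gamblers with co-occurring problem drinking, it is predicted that participants provided access to the G + A website will display significantly reduced gambling outcomes". The second reads "For problem gamblers without co-occurring problem drinking, there will be no significant difference between those provided access to the G-only and G + A websites". H2 has the same structure for drinking: "For problem drinkers, it is predicted that participants provided access to the G + A website will display significantly reduced drinking outcomes", with no difference expected in the others. The Abstract repeats the gambling prediction for co-occurring problem drinkers only. The Baseline survey section supplies the classifier, an AUDIT score of 8 or more.

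**Primary analysis (Data analysis).** The hypotheses are introduced as "The two primary hypotheses of this study, which focus on comparing outcomes between groups for gambling and drinking respectively" and are to be analysed with random-intercept linear mixed models, one per primary outcome. The section names no problem-drinking factor, subgroup or contrast for these models. Effect modification comes next, under secondary analyses, where "additional fixed-effect interactions will be included in exploratory models". The examples listed there include "severity of gambling and drinking at baseline".

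**Sample size (Power analysis).** The target is 280 randomised and 224 followed up. The section states 80% power at alpha 0.05 for a difference of two gambling days per month between the two conditions, and for one NODS point. It says this suffices to test the hypotheses. Problem drinkers are not mentioned there.

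**Expected mix (Participants; Discussion).** About half the sample is expected to have problem drinking. The Discussion cites a lifetime prevalence of 45% to 73%.

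**The concern.** The hypotheses ask whether the arm effect depends on problem-drinking status. A primary model that compares the arms without that status answers another question: whether the combined website is better on average in whatever mix of participants is recruited. If H1 is true, that average mixes a real effect with a zero effect.

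Two things are at stake. The first is interpretation. A whole-sample difference of a given size could come from a benefit confined to problem drinkers or from a smaller benefit in everyone, and the contrast cannot tell which. The second is power, because dilution shrinks the effect that the primary test has to find. The contrast that would answer the question would carry only exploratory status. The choice between whole-sample and subgroup results could then be made after they are seen.

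**Working it through.** **Inputs from the Protocol article.** 280 randomised, 20% attrition, power 0.80, alpha 0.05, a detectable difference of 2 days per month or 1 NODS point, and a problem-drinker share p of about 0.50. The sensitivity range for p is 0.45 to 0.73. That is lifetime prevalence, whereas the AUDIT used here covers the past 3 months, so the range is only indicative.

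**Assumptions.** 1:1 allocation, two-sided alpha, the same SD and attrition in both drinking groups, and no multiplicity adjustment. The article gives no SD.

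**1. The plan's own figures.** 280 × (1 − 0.20) = 224 completers, so 112 per arm, which reproduces. The 80% power cannot be reproduced without an SD, so it is taken as given and solved backwards. Effect divided by standard error must equal 1.960 + 0.842 = 2.802. The standard error of the whole-sample difference is therefore 2 / 2.802 = 0.714 days, and the effective SD is 0.714 / √(2/112) = 5.34 days (2.67 NODS points).

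**2. Whole-sample contrast if H1 is true.** With 2 days in a share p and 0 in the rest, the average difference is 2p and the noncentrality is 2.802 × p.
- p = 0.50: difference 1.0 day, 2.802 × 0.50 = 1.401, power Φ(1.401 − 1.960) = 0.29.
- p = 0.45: 0.9 day, power 0.24.
- p = 0.73: 1.46 days, power 0.53.

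All three differences lie below 2 days. The Power analysis section itself says that smaller differences may not be clinically meaningful.

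**3. Contrast within problem drinkers.** The effect stays at 2 days with 112p completers per arm, so the noncentrality is 2.802 × √p.
- p = 0.50: 56 per arm, 2.802 × 0.707 = 1.981, power Φ(1.981 − 1.960) = 0.51.
- p = 0.45: 0.47.
- p = 0.73: 0.67.

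Since √p exceeds p for any share below 100%, under H1 the subgroup contrast always has more power than the diluted one. As a cross-check, a repeated-measures F-test with two time points, set to 80% power at 224, gives 0.50 at 112 completers.

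**4. Arm-by-status interaction (2 days against 0).** The noncentrality is 2.802 × √(p(1 − p)).
- p = 0.50: 2.802 × 0.50 = 1.401, power 0.29.
- p = 0.45: 0.29.
- p = 0.73: 0.24.

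**5. What 80% power would take at p = 0.50.**
- Within problem drinkers, the detectable difference is 2 / √0.50 = 2.83 days, or 1 / √0.50 = 1.41 NODS points. To keep 2 days, 224 / 0.50 = 448 completers are needed, or 448 / 0.80 = 560 randomised.
- For the interaction, the detectable difference is 2 / √0.25 = 4.0 days. To keep 2 days, 224 / 0.25 = 896 completers are needed, or 896 / 0.80 = 1,120 randomised.

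**The case against.** The strongest reply is that the article never says the primary models compare the arms overall. It says that the hypotheses will be analysed, and the hypotheses are set out by drinking status. The groups being compared could be formed by arm and status together. The interactions called additional may be additional to ones already in the primary model. The listed moderator is drinking severity, which is not the same variable as the AUDIT cut-off, so a primary model with the binary status and an exploratory one with severity would fit the words. This is also a condensed article, and the fixed effects may be listed in a statistical analysis plan that is not shown.

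Much of this stands. A reader might infer that the plan fixes a whole-sample primary analysis and so certainly leaves H1 and H2 untested. The document does not support that much, because the fixed effects are not given and whole-sample is an inference. It is still the most natural reading. No sentence places problem-drinking status in a primary model, the only mention of baseline drinking as a moderator is in the exploratory tier, and the power statement rests on a two-arm difference in all completers. The point therefore concerns what the article states about tiers and power, and a missing list of model terms would not by itself be a finding.

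Two further inferences should be resisted. Naming the right contrast does not make the trial adequately powered: the subgroup contrast reaches only 0.51, and the interaction, at 0.29, does no better than the diluted whole-sample test. Nor is moderation by drinking left unexamined, since the exploratory models would estimate it. The dispute is over which result is confirmatory. Shares of problem drinkers below 45% would give lower power for both contrasts, but the article offers no basis for them.

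**Conclusion.** The concern holds as a mismatch between the conditional primary hypotheses and the primary analysis and power statement as described. That mismatch follows from the text alone and needs no SD. Its size does rest on assumptions: that the stated 80% power for 2 days is correct for 224 completers, plus those listed with the inputs. On that basis, if H1 is true with half the sample problem drinkers, a whole-sample primary test has power about 0.29 and the contrast within problem drinkers about 0.51. Over 45% to 73% the figures are 0.24 to 0.53 and 0.47 to 0.67. The statement that the sample size suffices for the hypotheses is supported for neither contrast. This changes what the trial can conclude, so it should be settled before outcomes are compared by arm.

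**What to change.** **Data analysis section.** Name the arm difference among participants with baseline AUDIT of 8 or more as the primary contrast for H1 and H2. Take it from a model with arm, visit, problem-drinking status and their interactions, or from equivalent stratified models. Report the arm-by-status interaction with its confidence interval as an estimate of differential effect. Keep continuous drinking severity as an exploratory moderator. If status was always meant to be in the primary model, one sentence saying so removes the ambiguity.

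**Power analysis section.** Restate the power for the chosen contrast and give the SD used. At a 50% share it is about 0.51 for 2 days or 1 NODS point. Equivalently, about 2.8 days or 1.4 points are detectable at 80% power. Disclose that the interaction has only about 0.29 power.

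**Cost.** Wording only, since baseline AUDIT is already collected. The downside is a less favourable stated power, which rewording cannot restore; only a larger sample of problem drinkers would.

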### Power analysis

Efforts will be made to recruit a total sample of 280 participants, and we anticipate that 224 participants will be successfully followed up at 6 months (i.e., estimated 20% attrition based on previous research of online interventions, albeit targeting hazardous alcohol use) [40]. This sample size will provide sufficient power to conduct the proposed statistical analyses necessary to test the aforementioned hypotheses. Based upon previous data collected by Hodgins et al. [4, 6] on gambling frequency and NODS scores, and assuming that a correlation of 0.5 exists between baseline and follow-up measures, then power = .0.80 and α = .05. This sample size is sufficient to detect a difference of at least two gambling days per month between both experimental conditions in both the 3- and 6-month follow-up periods. Smaller differences in gambling days per month may not be clinically meaningful. Similarly, the proposed sample size will also be sufficiently powered to detect a 1-point difference of NODS scores at the 6-month follow-up. Calculations are based upon a repeated measures ANOVA model (G.Power 3.1.9).

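### The primary mixed models name no baseline adjustment; a common baseline mean or a baseline covariate would cut the 6-month variance by about 21% at the plan's own correlation and attrition, if baseline is otherwise left free

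*Protocol article*

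**What the plan says.** The Data analysis section of the protocol article states that the first two hypotheses "will be analyzed using linear mixed-effect models with random intercepts", with a separate model for NODS, gambling days and drinks in a typical week. On missing data it adds: "This will allow us to use all available participant data within the models, employing a restricted maximum likelihood to handle missing data". It does not list the fixed effects, name the contrast to be tested, or say what role the baseline value plays. Baseline severity of gambling and drinking appears only among possible moderators, where "additional fixed-effect interactions will be included in exploratory models".

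The Power analysis section sets the stated power "assuming that a correlation of 0.5 exists between baseline and follow-up measures" and says that "Calculations are based upon a repeated measures ANOVA model". It gives neither a standard deviation nor the type of repeated-measures test. On sample size, "we anticipate that 224 participants will be successfully followed up at 6 months" out of 280 recruited.

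The Abstract (Methods) phrases the main prediction as a larger reduction at 6 months, and Major research questions describes the gambling outcomes as measuring reduction.

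**The concern.** Four features point the same way: outcomes worded as reductions, a repeated-measures power calculation that uses the correlation of baseline with follow-up, a model chosen for using all available data, and baseline severity placed only in exploratory interactions. Together they suggest that baseline, 3 and 6 months are all responses, with freely estimated means in each arm, and that the treatment effect is the arm-by-visit term. That term is a difference in change from baseline.

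In a randomized trial the true baseline means are equal across arms, so a model that estimates them separately gives up information. The cost depends on the correlation r. At r = 0.5, the plan's value, subtracting baseline adds as much noise as it removes, whereas conditioning on baseline only removes it. What is at stake is precision on all three primary outcomes, from data the trial already collects.

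**Working it through.** **Inputs from the protocol article (Power analysis).** 280 recruited, 224 followed at 6 months, r = 0.5, power 0.80 and α = 0.05. Detectable differences are 2 gambling days per month and 1 NODS point.

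**Assumptions.** Two-sided test; 1:1 allocation, so 140 per arm randomized and 112 followed; equal variance SD² at each visit and equal correlation r between visits, as a standard random-intercept model implies.

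**Plan's own figures.** 280 × (1 − 0.20) = 224, which agrees. The 0.80 cannot be reproduced because no SD is given. At 112 per arm, 80% power corresponds to a difference of (1.960 + 0.842) × √(2/112) = 0.374 SD for a contrast with variance factor 1.00. Two days would then imply an SD of 5.34 days, and 1 NODS point an SD of 2.67. With a factor of 0.75 the implied SDs are 6.17 and 3.08. The article does not show which was used.

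**Complete data, one follow-up visit.** Variance per person, in units of SD²:
- follow-up only: 1
- change from baseline: 2(1 − r) = 2 × 0.5 = 1.00
- baseline as covariate, or common baseline mean: 1 − r² = 1 − 0.25 = 0.75

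The saving against the change contrast is 25%.

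**Under the planned attrition.** Suppose the 28 people per arm who are lost give a baseline value only. The free-baseline mixed model still uses those values. Scaled to 112 per arm, the variance of its 6-month change contrast is (1 − r²) + (112/140)(1 − r)², and with a common baseline mean it is 1 − r².
- r = 0.5: 0.75 + 0.8 × 0.25 = 0.95, against 0.75. Saving 0.20/0.95 = 21%.
- r = 0.3: 0.91 + 0.8 × 0.49 = 1.302, against 0.91. Saving 30% (35% with complete data).
- r = 0.7: 0.51 + 0.8 × 0.09 = 0.582, against 0.51. Saving 12% (15% with complete data).

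A generalized least squares calculation for the three-visit model gives the same values. If half of the losses instead occur between 3 and 6 months, the result at r = 0.5 is 0.941 against 0.741, again 21%. For the average of the 3- and 6-month effects at r = 0.5, the saving is 29–30% with attrition and 33% with complete data.

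**Effect on a contrast with exactly 80% power (r = 0.5, with attrition).** The variance ratio is 0.75/0.95 = 0.789, with square root 0.889.
- Power: Φ(2.802/0.889 − 1.960) = Φ(1.19) = 0.88 (0.90 with complete data).
- Detectable difference: 2 × 0.889 = 1.78 days per month and 1 × 0.889 = 0.89 NODS points (1.73 and 0.87 with complete data).

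**The case against.** The strongest objection is that the premise is partly inferred. The article fixes a class of model, and a random-intercept model can carry a baseline covariate or a common baseline mean. Hypotheses 1 and 2 also predict arm differences at the follow-ups, which fits an adjusted comparison. A condensed article commonly leaves fixed effects to the full protocol or SAP. This stands as a limit: if the full plan already adjusts, nothing is gained. It does not remove the point, because the features the article does state favour an unadjusted change contrast.

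A reader might infer stronger claims, which the documents do not support:
- **That the baseline data are wasted.** A model with baseline as a response does use them. It draws on the baselines of people later lost, and for r above 0.5 the change contrast is more precise than follow-up values alone.
- **That 25% is a fixed saving.** It holds for one visit, complete data and r = 0.5 only.
- **That the stated 0.80 is wrong.** If it had relied on the 0.75 factor, a complete-data change contrast at r = 0.5 would have about 68%: Φ(2.802 × √0.75 − 1.960). Without the SD or the G*Power test type, this is only a conditional scenario.
- **That the random-intercept covariance is wrong.** Equal variances and correlations across visits are a restriction, but no figure in the article shows that these outcomes violate it.

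It is also fair to note that the article doubts the clinical importance of differences below two days per month. The useful gain is therefore higher power at two days, more than a smaller detectable difference.

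**Conclusion.** The point holds as an improvement at almost no cost, not as a demonstrated error. If arm means are left free at baseline, using a common baseline mean or baseline adjustment cuts the 6-month variance by about 21% at r = 0.5 with 20% attrition. Over r from 0.7 to 0.3, with or without attrition, the range is about 12% to 35%. At r = 0.5 with attrition, the saving is worth about 27% more participants (1/0.789 = 1.27), or 80% power becoming about 88%.

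These figures rest on 1:1 allocation, equal variance and correlation across visits, and the plan's own r. The power figure further assumes that the unadjusted contrast starts at exactly 80%. Both analyses are valid under randomization, so the difference is one of precision; no bias or inflated type I error is shown.

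**What to change.** For NODS, gambling days and drinks in a typical week, state in the primary analysis that visit is categorical and that baseline, 3 and 6 months are responses, with baseline means held equal across arms within each drinking stratum. The treatment effects are then the arm differences at 3 and 6 months. The alternative is to model the 3- and 6-month values with the baseline value by visit as a covariate. The common-mean form has the advantage of keeping people with no follow-up in the model. Keep REML. An unstructured covariance over the three visits is optional.

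State which model and which variance the 0.80 power refers to, with the SDs used. If the full plan already adjusts for baseline, one confirming sentence is enough.

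The cost is a few lines of text and a negligible loss of degrees of freedom, with no extra data. The choice should be fixed before outcome data are examined, so that it cannot be guided by results.

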### Study design and procedures

The proposed study is a two-arm double-blinded parallel-group RCT comparing two online interventions over a 6-month period: an intervention targeting gambling issues only versus one that contains interventions for hazardous alcohol consumption. Potential participants, who respond to the advertisement by clicking on the link or visiting the website, will be provided first with a brief description of the study prior to completing an eligibility screener. Individuals who are found to be eligible will be asked to provide contact information in the form of an email address. Subsequently, potential participants will be sent an email with a link to an online consent form. Participants will be asked to provide their telephone number and mailing address as additional contact information, as well as to provide permission for study staff to contact them via phone or mail for follow-up surveys if correspondence by email is unsuccessful. Those who complete the consent form and provide a real postal address will be sent a link to complete the baseline questionnaire and will be randomized into one of the two experimental conditions. Randomization will be stratified on age, sex, and prior use of treatment using an automatized algorithm to ensure a random distribution of prognostic indicators at baseline. To reduce attrition in the study, those who complete the baseline questionnaire and access the online intervention will receive a $10 Amazon.ca gift certificate. At 3 and 6 months post-randomization, all participants will receive an email request to complete a follow-up survey in the form of a hyper-linked web address. In addition, up to two email reminders for follow-up survey completion will be sent to participants to promote retention in the study. Furthermore, participants who complete the 3-month follow-up will be sent a $20 gift certificate and those who complete the 6-month follow-up will be sent an additional $30 gift (i.e., a total honorarium of $60 for each participant including the amount given at the baseline). Lastly, participants in both the G-only and the G + A interventions will receive an additional three emails encouraging the use of each respective intervention. See Fig. 1 for a Consort diagram summarizing the study design.

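### Random intercepts alone impose equal variance and equal correlation over baseline, 3 and 6 months; if that is wrong, tests of change from baseline can be mis-sized in either direction, most plausibly too liberal at 6 months

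*Protocol article*

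**What the plan says.** The protocol's Data analysis section states that the primary hypotheses "will be analyzed using linear mixed-effect models with random intercepts", and that all available data are used by "employing a restricted maximum likelihood to handle missing data". It adds: "Separate analyses will be conducted for each primary outcome variable". The same model therefore serves NODS, gambling days and weekly drinks. No random slope, residual structure or robust standard error is named. The section does not say whether baseline is a response or a covariate.

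There are three measurement times: baseline and two follow-ups ("At 3 and 6 months post-randomization, all participants will receive an email request"). The Power analysis section works from a repeated measures ANOVA, "assuming that a correlation of 0.5 exists between baseline and follow-up measures", and expects 20% attrition. It gives no standard deviation for any visit and no correlation between 3 and 6 months.

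The abstract and the Major research questions section describe the gambling outcomes as reductions. The hypotheses themselves compare the arms at the 3- and 6-month follow-ups.

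**The concern.** A random intercept with independent residuals implies compound symmetry: one variance at every visit and one correlation for every pair. There are grounds to doubt this here. Baseline is selected (gambling in the past 30 days, PGSI of 3 or more) and precedes the intervention; both follow-ups come after it and carry no such restriction. A participant who has stopped gambling by 3 months may well still be abstinent at 6 months, so the two follow-ups may correlate more with each other than with baseline.

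Two things are at stake. First, the error rate and interval width of the primary tests, if these concern change from baseline. Second, the protection that REML gives against missing data: under missing-at-random dropout, likelihood estimates are generally consistent only if the covariance model is right as well as the mean model.

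**Working it through.** **The plan's own figures.** 224 / (1 - 0.20) = 280, so the attrition step reproduces. The stated power does not, because no SD is given. With 112 per arm (1:1 assumed), two-sided 5% and 80% power, and a change score at correlation 0.5 (so that the SD of change equals the SD), the largest SD consistent with a 2-day difference is 2 / (2.80 x sqrt(2/112)) = 5.34 days. For 1 NODS point it is 2.67. These serve only to put SD units on the outcome scale below.

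**Inputs.** From the protocol: three visits, a correlation of 0.5 between baseline and each follow-up, alpha 0.05 (sidedness not stated; two-sided assumed). Not in the protocol, hence assumed: the 3-to-6-month correlation, and the SD at each visit.

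**Formula.** With complete data and separate means by arm and visit, the random-intercept fit gives residual variance = mean variance - mean covariance, and takes the variance of any change as twice that. The true variance of change from baseline to visit j is V0 + Vj - 2 Cov(0,j). Let k be the square root of model variance over true variance. The actual size of a nominal 5% test is 2 x (1 - Phi(1.96 k)).

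**Equal SDs, 0.5 with baseline, r between follow-ups.** Mean correlation is (0.5 + 0.5 + r)/3. For r = 0.7 it is 0.5667, so the residual variance is 0.4333 and the model variance of change is 0.867, against a true 1.00. Hence k = 0.931 and the size is 6.8%.

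| r (3 to 6 months) | model variance | k | size |
|---|---|---|---|
| 0.4 | 1.067 | 1.033 | 4.3% |
| 0.5 | 1.000 | 1.000 | 5.0% |
| 0.6 | 0.933 | 0.966 | 5.8% |
| 0.7 | 0.867 | 0.931 | 6.8% |
| 0.8 | 0.800 | 0.894 | 8.0% |

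**Other structures.**
- Decaying correlation (0.7 for adjacent visits, 0.5 for baseline to 6 months): model variance 2 x (1 - 0.6333) = 0.733. True variance is 0.60 at 3 months (k = 1.106, size 3.0%) and 1.00 at 6 months (k = 0.856, size 9.3%).
- All correlations 0.5, follow-up SD 20% lower: model 0.773, true 0.84, size 6.0%.
- All correlations 0.5, follow-up SD 20% higher: model 1.307, true 1.24, size 4.4%. With that higher SD and r = 0.6 / 0.7 / 0.8, the size is 5.3% / 6.3% / 7.6%.

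**Arms compared at one visit, baseline still a response.** The model variance is intercept plus residual = mean covariance + (mean variance - mean covariance) = mean variance. With equal variances and complete data this is correct for any correlation.

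**Size with missing data.** A simulation with 140 per arm, 15% missing at 3 months and 20% at 6 months gave, for 6-month change at r = 0.7 and 0.8, sizes of 5.6% and 6.7% with random intercepts. An unstructured covariance gave 4.8% to 5.2% (Monte Carlo error about 0.4 to 0.5 points). Dropout thus dilutes the closed-form figures somewhat.

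**Bias under dropout.** A large-sample simulation used 20% loss at 6 months that depended on the 3-month value (logistic slopes, SD units). With compound symmetry true, there was no detectable bias. With it false but the same dependence in both arms, bias was again about zero. With dependence in one arm only, it was 0.005 to 0.027 SD. With opposite slopes (+1 and -1), it was 0.018 to 0.061 SD, the largest value arising at r = 0.7. On the SDs above, 0.06 SD is 0.06 x 5.34 = 0.32 days or 0.06 x 2.67 = 0.16 NODS points, 16% of the target difference in each case.

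**The case against.** The strongest reply has four parts.

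1. *The tested contrast is inferred.* The hypotheses compare arms at follow-up, and no section says that baseline is a response. With baseline as a covariate only two response visits remain, their correlation is estimated freely, and the only constraint is equal variance at 3 and 6 months. This stands as a condition on the point. Against it, the protocol describes outcomes as reductions, uses a repeated measures power model and mentions no baseline covariate.

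2. *The direction is not known.* A reader might infer that the standard errors are simply too small and that the tests reject too often. The protocol does not support that: the 3-to-6-month correlation is not given, and the calculations include conservative cases (4.3%, 4.4%, 3.0%) and one with no distortion. The eligibility floor may also narrow the baseline spread, which pushes the other way. A reader might likewise compute the average of both follow-ups against baseline, where the inflation is larger (6.7% / 8.7% / 11.0% at r = 0.6 / 0.7 / 0.8), but the protocol specifies no such contrast.

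3. *The dropout bias is a corner case.* It needs a wrong covariance and, in the scenarios tested, outcome-dependent dropout that differs by arm. This stands.

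4. *Residual structure belongs in the statistical analysis plan.* A random intercept does not exclude an added residual structure, and the analysis plan is not at hand. If it sets one that frees the covariance, the point is met. But the protocol does state random intercepts as the method; this is a choice to be judged, not a detail left open.

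**Conclusion.** The point holds as a conditional one. The stated model imposes compound symmetry unless a residual structure is added, and the protocol's single value of 0.5 says nothing about the correlation between the follow-ups. For tests of change from baseline, the actual size of a nominal 5% test runs from 3.0% to 9.3% over the structures examined. The most plausible departure, follow-ups correlating at 0.6 to 0.8, gives 5.8% to 8.0% at 6 months with complete data and equal SDs, and somewhat less with the expected dropout. These correlations are assumptions.

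A claim that the primary tests are liberal in general, or that the 6-month estimate will be biased, would go beyond the document. The case for a change is that the model's validity rests on an assumption that the protocol neither supports nor needs.

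**What to change.** In the Data analysis section, replace the random-intercept phrase by: *with visit as a categorical factor and an unstructured within-person covariance over baseline, 3 and 6 months (REML, Kenward-Roger degrees of freedom)*. Apply it to NODS, gambling days and weekly drinks. In the same sentence, say whether baseline is a response and whether the tested contrast is change from baseline or the arm difference at a visit.

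If the model fails to converge, fall back on a simpler structure with robust (sandwich) standard errors. A Toeplitz structure, even with unequal variances, should not be presented as capturing a higher 3-to-6-month correlation, since it sets the baseline-to-3-month and 3-to-6-month correlations equal. Robust standard errors repair the size of the test but not bias under dropout.

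The cost is six covariance parameters instead of two, which is negligible with about 280 participants, and a small risk of non-convergence. The change remains valid if compound symmetry turns out to be true.
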